### Consent and baseline assessment

After the potential participant has had adequate time to consider involvement in the study, she will be contacted by a member of the trial team to ascertain interest in the trial. The consent, baseline assessment and randomisation for STOPPIT-3 are anticipated to be combined and conducted as a single visit before the planned birth and will wherever possible coincide with routine preadmission appointments to help minimise additional visits. Written informed consent will be taken by a member of the maternity care team. Consent should be provided within 7 days of randomisation/investigational medicinal product (IMP) administration. The original signed consent form will be stored in the Investigator Site File, with a copy given to the woman and a copy added to the medical notes. The women’s demographics, medical history, obstetric history, current pregnancy information and inclusion/exclusion criteria will be collected and entered on the electronic case report form (eCRF) by a member of the trial team. The inclusion/exclusion criteria will be further assessed by a doctor (delegated by the principal investigator (PI)) and they will complete and sign the eligibility form confirming the woman meets the study criteria to participate and is suitable for randomisation. A letter will be sent to the registered general practitioner to inform them of the woman’s participation in the trial.

### Randomisation

Randomisation to ACS or placebo will be performed immediately prior to administration, 24 hours to 120 hours before the planned birth. Randomisation is performed using a web-based randomisation system managed by Edinburgh Clinical Trials Unit (ECTU) via a web portal. Users will be assigned a unique study identifier and will be required to enter minimal patient details prior to randomisation. As this is a large trial (1552 women), group imbalances are unlikely therefore a simple allocation sequence with no minimisation criteria will be used. Study participants, trial investigators and medical staff providing care will remain blinded to treatment allocation. The randomisation process will assign each participant with a study drug treatment pack number and the first dose of IMP should be given immediately following randomisation with the second dose administered 24 hours (±4 hours) after the first dose. Participants will be allocated to receive either:

Corticosteroid group—two doses of 12 mg dexamethasone by IM injection 24 hours (±4 hours) apart.Placebo group—two doses of matching placebo (sodium chloride 0.9%) by IM injection 24 hours (±4 hours) apart.

### Data collection and management

Birth and neonatal information will be extracted from the woman’s±babies’ medical notes and information recorded in the eCRF by a member of the maternity research team. Trial data will be collected by members of the maternity care team delegated by the PI. A unique trial identifier will be allocated to each participating woman at randomisation and this unique number will be used for data collection within the trial. Identifiers will be stored in separate tables from the main data tables within the trial database and only delegated members of the team will be granted access to these tables (see Data Sharing Plan, (online supplemental material).

10.1136/bmjopen-2023-078778.supp1Supplementary data

### Long term follow-up assessments

The first 340 STOPPIT-3 participants recruited will be asked to complete the PARCA-R questionnaire (online or paper copy) at 2 years (to assess the cognitive and language development).

### Statistical analysis and sample size

The statistical analysis will be according to the intention to treat principle (ie, all participants will remain in their allocated group for analysis). Statistical significance will be at the 5% level with corresponding 95% CI presented. Randomised groups will be described at baseline and follow-up using mean (SD), median (IQR) and counts (with percentages) as appropriate.

For the primary outcome (respiratory support within 72 hours of birth), the OR (and 95% CI) for the treatment effect of ACS will be estimated adjusting for mode of delivery, treatment centre (if appropriate) and chorionicity with logistic regression. To account for the clustering effect within twin pairs, a random-effects logistic regression model will be used by fitting pregnant woman as a random effect.

Continuous secondary outcomes will be analysed using linear regression, and binary categorical secondary outcomes will be analysed using logistic regression as per the primary outcome. Secondary outcomes with more than two categories will be analysed using multinomial logistic regression.

Subgroup analyses, for example by sex of twins, chorionicity and presence of maternal comorbidity (eg, hypertension) will be considered.

No interim analyses are planned other than re-estimation of the intraclass correlation (ICC, assumed to be 0.3) following the internal pilot. This will be done by estimating the 95% CI (without, and possibly with, adjustment for covariates) as per the event rate around the observed ICC at 200 women with complete data, and if this 95% CI does not contain 0.3 corrective action will be taken.

We plan to recruit 1552 women randomised at 1:1 to ACS or placebo prior to planned birth. We will have 90% power at the 5% significance level to detect a relative difference in the neonatal primary outcome of respiratory support within 72 hours of birth between the groups of 33% (absolute difference of 4%) assuming an event rate of 12% in the placebo group and an ICC of 0.3, assuming 1% of missing data for the primary outcome.

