### Eligibility criteria

The following inclusion criteria will apply at the screening assessment (all must apply):

Aged 16 years or older and able to provide electronic or written consent.Viable twin pregnancy (MC or DC) with a planned birth* scheduled between 35+0 and 38+6 weeks gestation including women who have a planned birth due to logistic reasons (eg, availability of beds or staff), parental preference or other maternal or fetal indications.Gestation established by scan at≤16 weeks according to NICE guidelines and known chorionicity.≥24 hours* and<7 days until planned birth.*Birth must be planned to take place at 35 or more weeks gestation, after IOL or CS. At the point of randomisation, there must be ≥24 hours until the planned CS or IOL date to allow two doses of the study drug to be administered, at 24 hours (±4 hours) apart prior to the planned birth.

The following exclusion criteria will apply:

Unable to give informed consent.Known or suspected major congenital fetal anomaly at the time of inclusion (defined as any structural or chromosomal anomaly that would influence management at or around birth or in the immediate postnatal period. Suspected isolated minor anomalies with lesser medical, functional or cosmetic consequences; or isolated limb abnormalities such as talipes can be included).Diabetes (pre-existing or gestational)—corticosteroid use may significantly disrupt glycaemic control in women with diabetes, with potential to ‘unblind’ treatment allocation and pose risk to these women. The effect of corticosteroids prior to planned CS in women with diabetes will be examined in other studies.Receipt of ACS within the 7 days prior to randomisation.Sensitivity, contraindication or intolerance to any of the ACS or any of its excipients.Chorionicity or gestational age are unknown.Other serious pregnancy morbidities which indicate either birth before 35 weeks or urgent birth within 24 hours.

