### Health economic analysis

The primary within trial analysis will be a cost-effectiveness analysis which will estimate the incremental cost per reduction in respiratory support (initiated within 72 hours after birth, ie, the study primary outcome), with the time horizon spanning from birth to child hospital discharge or 28 days, whichever is sooner.

The costs of the intervention will be calculated as the daily cost of ACS medication and the associated administration costs. Hospital attendances required to administer ACS will be included. The direct medical costs post birth will be calculated based on resource utilisation accruing for the care of new born (after birth respiratory treatment; admission to neonatal care) and women (type of delivery, inpatient stays; hospital transfers, etc) including adverse events. Resource utilisation for woman and child will be collected from the clinical hospital records up to 28 days post birth.

The mean cost and mean outcome associated with the intervention and the control arm will be estimated using generalised linear model, which will tackle non-normality of data, adjusting for relevant covariates (eg, type of delivery; MC/DC twins) and adjusting for women-level clustering, in line with the statistical analysis.

If evidence of differences between the treatment arms in terms of effectiveness, costs or cost-effectiveness are found in the trial, a decision analytic model will be developed to explore the cost-effectiveness of ACS administration over a medium (2 year) and longer term (lifetime) horizon. The medium term analysis will use data from the final trial follow-up period in childhood (eg, PARCA-R, any medical records available, etc), to account for costs and consequences which are associated with ACS treatment over the neonatal period (hypoglycaemia; neonatal health) and childhood (mortality; cognitive development metabolic illness).

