### Ineligible and non-recruited participants

Women who consent to participate in the study, but who spontaneously give birth or undergo IOL or CS prior to randomisation will not be eligible for randomisation. Such women who did consent to participate will be withdrawn but will remain on the eCRF system and reported in recruitment metrics as ineligible post consent. No delivery outcomes will be collected and they will continue receiving standard care under the management of a clinician, as per current guidelines. The woman’s care will not be affected due to non-trial participation. Randomisation and IMP administration should be performed contiguously to minimise the chance of spontaneous labour or delivery between randomisation and IMP administration.

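### The primary model adjusts for mode of delivery, which as written is settled only after randomisation and dosing; planned mode at randomisation should replace it, in the cost model as well

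*Protocol article*

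**What the plan says.** All places are in the protocol article.

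- **Statistical analysis and sample size.** The odds ratio for ACS on respiratory support within 72 hours "will be estimated adjusting for mode of delivery, treatment centre (if appropriate) and chorionicity with logistic regression". A random effect for the woman is added. Binary secondary outcomes take the same form. The analysis is by intention to treat, explained there as every participant staying in the allocated group.
- **Randomisation.** "Randomisation to ACS or placebo will be performed immediately prior to administration, 24 hours to 120 hours before the planned birth", and "the first dose of IMP should be given immediately following randomisation".
- **Eligibility criteria.** "At the point of randomisation, there must be ≥24 hours until the planned CS or IOL date". The planned route and date are therefore known at entry.
- **Ineligible and non-recruited participants.** Randomisation and dosing are kept close together "to minimise the chance of spontaneous labour or delivery between randomisation and IMP administration", so the article itself foresees births that depart from the plan.
- **Data collection and management.** "Birth and neonatal information will be extracted from the woman’s±babies’ medical notes".
- **Health economic analysis.** The resource use to be costed includes that of "women (type of delivery, inpatient stays; hospital transfers, etc) including adverse events". Mean cost and mean outcome are then estimated with a generalised linear model, "adjusting for relevant covariates (eg, type of delivery; MC/DC twins) and adjusting for women-level clustering", said to be in line with the statistical analysis.

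Nowhere is mode or type of delivery defined as the mode planned at randomisation.

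**The concern.** Chorionicity and centre are fixed before allocation. Actual mode of delivery is not: it is determined days after randomisation and after at least the first dose. A planned induction may end vaginally or by caesarean, and labour may start before a planned caesarean.

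Adjusting for a variable of this kind has two possible consequences:

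1. If ACS changes mode, and mode affects the need for respiratory support, that part of the treatment effect is removed from the estimate.
2. If some unmeasured factor, such as fetal condition in labour, influences both mode and outcome, then comparing arms within mode can compare women who are no longer alike.

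At stake is what the primary odds ratio, and those for the binary secondary outcomes, estimate. The analysis would still keep every woman in her allocated group, but its result would not be guaranteed to be the total effect of being allocated to ACS.

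In the cost model the same variable appears on both sides, inside the cost and among the covariates. Any cost difference that treatment produced by changing type of delivery would be adjusted away.

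**Working it through.** **1. Which mode is meant?** At randomisation the known facts are a planned CS or IOL and its date. IOL is not itself a mode of delivery. The article uses the word planned freely elsewhere (planned birth, planned CS) but not for this covariate. In the economic section, type of delivery is resource use taken from hospital records, so there it must be what actually happened. The same term then serves as a covariate, with an explicit link to the statistical analysis. Actual mode is the natural reading.

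**2. Does the sample size depend on it?** Inputs from the article: 12% against 8%, 5% significance (two-sided assumed, since sidedness is not stated), 90% power, intraclass correlation 0.3, 1% missing.

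- Babies per arm, pooled variance: [1.960 × √(2 × 0.10 × 0.90) + 1.2816 × √(0.12 × 0.88 + 0.08 × 0.92)]² / 0.04², rounded up to 1181.
- Design effect for pairs: 1 + (2 − 1) × 0.3 = 1.3, and 1181 × 1.3 = 1535.3, rounded up to 1536 babies per arm. With two babies per woman and two arms, this is 1536 women in total.
- Missing data: 1536 / 0.99 = 1551.5, rounded up to **1552**, the article's figure.

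The calculation is an unadjusted comparison of two proportions. Changing or dropping the covariate leaves it unchanged.

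**3. How far could the odds ratio move?** The documents give no figure for the effect of ACS on mode, so what follows is illustration under assumptions made for this review. Each set-up compares the odds ratio without mode (total effect) and with actual mode in the model. Both use a 12% placebo event rate.

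*Set-up A.* 60% CS under placebo; an unmeasured factor with 30% prevalence and odds ratio 2 on both mode and outcome; CS multiplies the odds of respiratory support by 2 or 3; direct ACS odds ratio (0.08/0.92)/(0.12/0.88) = 0.638. ACS either leaves CS unchanged or makes it less frequent.

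| ACS odds ratio on CS | Total effect (CS effect 2; 3) | Adjusted for actual mode |
|---|---|---|
| 1.00 | 0.644; 0.647 | 0.641; 0.641 |
| 0.90 | 0.634; 0.633 | 0.643; 0.643 |
| 0.80 | 0.623; 0.617 | 0.645; 0.645 |
| 0.67 | 0.606; 0.592 | 0.648; 0.648 |

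Here adjustment understates benefit, by at most 0.648 − 0.592 = 0.056.

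*Set-up B.* 21% unplanned CS under placebo; an unmeasured factor with log odds ratio 1 per SD on both unplanned CS and outcome; CS doubles the odds of support; direct ACS odds ratio 0.60. ACS either leaves unplanned CS unchanged or makes it more frequent.

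| Unplanned CS under ACS | Total effect | Adjusted for actual mode |
|---|---|---|
| 21% | 0.64 | 0.63 |
| 24% | 0.66 | 0.61 |
| 27% | 0.67 | 0.59 |
| 32% | 0.70 | 0.57 |

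Here adjustment overstates benefit, by up to 0.70 − 0.57 = 0.13. Halving the unmeasured log odds ratio to 0.5 cuts the gap at 32% from 0.13 to about 0.08, and at 24% from about 0.05 to about 0.03.

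The small gap in the first row of each table arises with no effect of ACS on mode. It reflects the odds ratio being non-collapsible, which a legitimate baseline covariate would show as well.

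**4. Cost.** Take an additive cost model in which CS costs D more than the alternative, and suppose ACS changes the CS proportion by δ. The incremental cost then contains δ × D. With actual type of delivery as a covariate, that term is carried by the covariate and leaves the treatment coefficient. If δ = 0, nothing is lost by this route.

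**The case against.** The strongest reply is that this is loose wording in a condensed article. Every woman in the trial has a planned CS or IOL, the other two covariates are baseline variables, and the authors may have meant planned route, which would be a sound covariate. That possibility stands. But the text does not say so, and the economic section's use of the term points to the actual event. The wording needs correcting on either reading.

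The second reply concerns harm. Material bias requires ACS to change mode, and nothing in the documents says that it does. This also stands, and it limits what may be claimed. A reader might infer any of the following, and the documents support none of them:

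- **That the randomised comparison is broken.** With no effect of ACS on mode, the odds ratio barely moves in either set-up.
- **That adjustment overstates benefit.** It does so in one set-up and understates it in the other. The direction follows from the assumptions chosen.
- **That incremental cost is biased by construction.** Overlap between a costed item and a covariate matters only if treatment shifts type of delivery, or through selection on mode. The covariate is also given only as an example, so this half is less firm than the primary model.
- **That the twins of a pair may be delivered by different modes.** The documents do not say this, and the point does not need it.

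**Conclusion.** The concern holds in limited form. As written, the primary model and the binary secondary models condition on a variable settled after randomisation and dosing, so their odds ratios are not guaranteed to be total effects of allocation. The cost model, if it uses its example covariate, would remove any delivery-cost difference that treatment caused.

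The size cannot be fixed from the documents. It is negligible if ACS does not alter mode. If it does, the illustrations give shifts from about 0.01 to 0.13 on the odds-ratio scale, in either direction, depending on unsourced assumptions about the effect on mode and the strength of shared causes. Because the direction is unknown, a reader of the results could not correct for it afterwards. The case for change rests on the estimand being wrongly specified and easily put right, not on a demonstrated large bias.

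**What to change.** - **Primary model, and the binary secondary models that follow it:** replace mode of delivery with *planned mode of birth at randomisation (planned CS or planned IOL)*.
- **Cost and outcome model:** use the same planned-mode variable as the covariate, and keep actual type of delivery as a cost item only.
- **Actual mode:** report it descriptively by arm, or adjust for it only in a labelled sensitivity analysis.

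The cost is one line in each of the two analysis sections, made before unblinding. Eligibility already requires the planned CS or IOL date, so the information exists at entry; the team should confirm that the planned route is held as its own field in the case report form. No further participants are needed, and the target stays at 1552 women.

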## Introduction

The overall aim of STOPPIT-3 is to address the uncertainty regarding the effectiveness of antenatal corticosteroids (ACS) prior to a planned birth of twins in the late preterm and early term period. ACS are widely administered via intramuscular (IM) injection to women at risk of preterm birth (defined as birth less than 37 completed weeks gestation) to reduce morbidity and mortality in babies born too early^1^ and have been recommended since the 1990s. ACS are known to be most effective if birth occurs 24–48 hours following administration of the first dose, with little or no benefit seen if birth is 7 days or more after administration.^1^

Twin pregnancy is common and associated with adverse outcomes for the babies, accounting for ~3% of live births but ~15%–20% of all neonatal care admissions.^2^ 2019 NICE guidance for twin pregnancy recommends planned birth at 37+0 weeks gestation in uncomplicated dichorionic (DC) twins (twins that have separate placentae), and planned birth at 36+0 weeks gestation in uncomplicated monochorionic (MC) twins (twins that share a placenta (~20% of twins)).^3^ Planned birth is by induction of labour (IOL) or caesarean section (CS). These slightly earlier, non-spontaneous births are at increased risk of respiratory morbidity and needing respiratory support requiring neonatal care admission.

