There is, however, currently little evidence that ACS are as effective in twins, and similarly little evidence that ACS are effective in the late preterm and early term period which is the period that NICE recommend that twins are born.^3^ Evidence as to whether women having planned birth of twins should receive ACS is both conflicting and confusing, with practice known to be highly variable across the UK in this area. ACS are widely given to women with twin pregnancies having planned birth, despite recognition that ACS *may* have adverse effects on growth and neurodevelopment.^4 5^ There is some evidence that ACS in singleton pregnancies in the late preterm period (34+0–36+6 weeks) and/or prior to planned CS at term (37+0–38+6 weeks gestation)^6^ may have short-term benefits reducing respiratory morbidity and neonatal care admission. This evidence is often extrapolated to twin pregnancy, however, there is almost no evidence showing benefits of ACS from women with twin pregnancies. Differences in the pharmacokinetics of ACS,^7^ and mechanisms of fetal maturation (which may be accelerated in twins),^8^ may mean that ACS have different effectiveness at late preterm and early term gestations.

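### The primary model leaves out gestational age, a covariate known before randomisation; adding it would be a small, nearly free gain in precision

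*Protocol article*

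**What the plan says.** Under Statistical analysis and sample size, the protocol article fixes the covariates of the primary analysis: the odds ratio is estimated "adjusting for mode of delivery, treatment centre (if appropriate) and chorionicity with logistic regression". For twin clustering, "a random-effects logistic regression model will be used by fitting pregnant woman as a random effect". Binary secondary outcomes follow the same approach. Only centre is conditional; the list is not offered as an example.

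Four other places bear on gestation:
- Eligibility criteria: entry requires a "planned birth* scheduled between 35+0 and 38+6 weeks gestation".
- Eligibility criteria: entry also requires "Gestation established by scan at≤16 weeks according to NICE guidelines and known chorionicity", and unknown gestational age is an exclusion.
- Introduction: "These slightly earlier, non-spontaneous births are at increased risk of respiratory morbidity". The same section cites guidance for planned birth at 37+0 weeks in uncomplicated dichorionic twins and 36+0 weeks in uncomplicated monochorionic twins, the latter about 20% of twins.
- Randomisation: "a simple allocation sequence with no minimisation criteria will be used", on the ground that the trial is large.

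**The concern.** Gestation at randomisation is fixed before treatment and should be known for every woman. On the protocol's own account, earlier planned birth goes with the kind of morbidity that the primary outcome measures. Neither the allocation method nor the model uses it.

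Chorionicity stands in for gestation only in part. The 36+0 and 37+0 recommendations are for uncomplicated pregnancies, whereas the eligibility criteria also admit births planned for logistic reasons, parental preference or other maternal or fetal indications. Gestation will therefore vary within each chorionicity group.

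Two things are at stake: some precision in the primary odds ratio, and protection of that estimate against a chance difference in gestation between the arms.

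**Working it through.** **1. The plan's own figure.** Inputs from Statistical analysis and sample size: 12% v 8%, 90% power, 5% significance (taken as two-sided), ICC 0.3, 1% missing.
- Babies per arm, pooled-variance formula: [1.960·√(2·0.10·0.90) + 1.282·√(0.12·0.88 + 0.08·0.92)]² / 0.04² = just over 1180, rounded up to 1181.
- Design effect for pairs: 1 + (2 − 1)·0.3 = 1.3.
- Women per arm: 1181·1.3/2 = 767.7, so 768; total 1536.
- Missing data: 1536/0.99 = 1551.5, so 1552.

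The target reproduces. It uses no covariates, so adding or omitting gestation does not change it.

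**2. Precision gained by adding gestation to a model that already has chorionicity.** The article gives no risk gradient per week, so the slopes and the spread of gestation are assumptions.

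*Random-intercept logistic model, as the plan specifies.* 1552 women; 20% monochorionic centred at 36.1 weeks, dichorionic at 37.1 weeks; within-group SD 0.7 or 1.0 week; 12% v 8%; ICC 0.28 to 0.31; 250 simulated trials per row. The information ratio is the squared ratio of mean z with and without gestation. Power is scaled from 90%, because raw simulated power carries a Monte Carlo error of about 2 points.

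| Assumed OR per week | Information ratio, SD 0.7 / 1.0 | Power, SD 0.7 / 1.0 |
|---|---|---|
| 0.8 | 0.999 / 1.005 | 90.0% / 90.1% |
| 0.65 | 1.007 / 1.006 | 90.2% / 90.2% |
| 0.5 | 1.020 / 1.029 | 90.6% / 90.8% |
| 0.35 | 1.052 / 1.079 | 91.4% / 92.0% |

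The treatment estimate hardly moves; the gain comes from the standard error. At OR 0.5 and SD 1.0 the mean log OR is −0.656 in both models, and its SE falls from 0.2016 to 0.1986.

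*Logistic regression with standard errors clustered on the woman.* 1536 women, 1500 simulated trials per scenario, ICC about 0.34, 20% monochorionic mostly at 36 weeks, dichorionic mostly at 37. Control risk was assumed to fall from 35 to 38 weeks by 19% to 8%, 23% to 6%, or 29% to 4%. Information rises by 0.5%, 2.4% and 4.8%. Times 1536, that is worth about 8, 37 and 74 women.

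**3. From information to power.** At 90% power the expected z is 1.960 + 1.282 = 3.24. A relative information r gives power Φ(3.24·√r − 1.96):
- r = 1.005: Φ(1.290), about 90.1%, a gain of 0.1 point.
- r = 1.024: Φ(1.320), about 90.7%, a gain of 0.7 point.
- r = 1.048: Φ(1.358), about 91.3%, a gain of 1.3 points.
- r = 1.08: about 92.1%, a gain of 2 points.

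**4. Chance imbalance.** Assume an SD of 0.8 week within chorionicity groups. The SE of the difference between arms in mean gestation is 2·0.8/√1552 = 0.041 week, so the 95% range is about ±0.08 week, or ±0.6 day. At OR 0.5 per week this moves the log OR by up to 0.693·0.08 = 0.055. At OR 0.35 it is 1.05·0.08 = 0.084. The random-intercept log OR for treatment is about −0.65 in these simulations, so the shifts are about 8% and 13% of the effect.

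**The case against.** The strongest case against is that this is only an optional refinement. The Introduction states the gestational risk qualitatively and gives no gradient within 35+0 to 38+6 weeks. The four-week span is the eligibility limit, and planned births will probably cluster near the guideline dates, where chorionicity already carries part of the information. A gain above 5% needs a very steep slope. With 1552 women, imbalance is likely to stay within about half a day. All of this stands, and it is why the size given here is small. It does not remove the point: the covariate list is stated, not left open, and the omitted variable is a clean baseline one.

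A reader might infer more, in four ways that the article does not support:
- *That the primary comparison is biased or the sample size wrong.* Omitting a baseline covariate does not bias a randomised comparison, and the 1552 does not depend on it.
- *That gestation is the trial's declared key risk factor.* The article never says so.
- *That the rationale raises a late-preterm versus early-term question which then goes unanalysed.* The Introduction says that differences in pharmacokinetics and fetal maturation "may mean that ACS have different effectiveness at late preterm and early term gestations". The sentence before it concerns extrapolating singleton evidence to twins, so in context the contrast is mainly twins against singletons.
- *That gestation is wrongly missing from the subgroups.* The text reads "Subgroup analyses, for example by sex of twins, chorionicity and presence of maternal comorbidity (eg, hypertension) will be considered". That list is illustrative, and its final form is commonly left to the SAP, which is not at hand.

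**Conclusion.** The point holds as a modest improvement to a stated analysis choice. The primary model omits a baseline covariate that is known for every woman, that the protocol ties to respiratory risk, and that the allocation does not balance. Under the assumed slopes, adding it brings about 0.5% to 5% more information: under 1% for weak gradients and up to about 8% for a very steep one. That is roughly 0.1 to 1.3 power points, and at most about 2. It also guards against a chance imbalance that is likely to be small. These figures depend on the assumed gradient and spread of gestation, which the article does not give. The validity of the trial, its test of treatment and its target of 1552 are not in question.

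**What to change.** Add gestational age at randomisation, in days, to the primary model and to the secondary models that follow it. Keep it continuous, as a linear term or a restricted cubic spline, and settle the choice before unblinding. State that gestation at actual birth is not to be used, because it is determined after randomisation.

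The cost is a change of wording and one extra model term (a few for a spline). No new assessment should be needed. The article does not itemise gestation at randomisation as a data field, but it follows from the required dating scan and the randomisation date, and it plausibly falls within the pregnancy information entered on the eCRF. The sponsor should confirm that it can be derived for every woman.
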